### Statistical analysis

Between group differences for primary and secondary outcome measures will be analysed using analysis of covariance (ANCOVA), suitable for use when extraneous factors need to be controlled.

Multivariate regression modelling will be used to examine predictors of successful response to intervention [43]. Potential predictors measured at baseline are personal characteristics, self efficacy beliefs, sub-domains of perceived health status, functional performance and disability levels whilst clinical improvements in NEADL and LLDI will be inputted as the dependant variable.

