### Outcome measurement

Data will be directly collected from medical records, participant self-report, calendars, standardised functional assessments and data linkage.

Participant self-report and medical records will be used to identify suitability for inclusion. Baseline assessments will then be completed by a research assistant with the participant in hospital. This assessment will involve functional questionnaires, demographic information, health related quality of life and falls history/self efficacy. Each baseline assessment will take approximately one hour to complete. These assessments will be completed again at three months after discharge from hospital by a blinded research assistant with the participant in their own home.

At discharge, all participants will receive a set of monthly calendars and a community health service use diary. Participants will be asked to record daily if they have a fall or not or if they use any community health services for three months after hospitalisation. Participants will be telephoned fortnightly post-discharge to follow up on any falls, community health service use, nursing care facility admission, and any out of pocket expenses to enhance accuracy of data. Participants will be prompted to return these to research staff during their final assessment. The assessments and telephone calls will be completed by a research assistant blinded to group allocation.

Primary outcome measures: Functional independence will be assessed using the Nottingham Extended Activities Daily Living scale (NEADL) [36] while participation and limitation in activities of daily living will be assessed using the Late Life Disability Index (LLDI) [37]. These assessments will be completed at baseline and three months post-discharge from hospital.

Secondary outcome measures: Fear of falling during activities of daily living will be measured using the International Falls Efficacy Scale (FES-I) [38]. Physical activity will be measured using the question “do you get out of the house as often as you like?” (used previously in a trial) [39] and the physical activity sub-scale of the SF-36v2 [40]. Health related quality of life will be assessed using the SF-12v2 [40]. Falls and community health service use will be recorded using a monthly self report falls calendar and diary.

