### Sample size calculation

A total of 400 participants will enter this two-armed, parallel-design study (200 per group). The probability is 80% that the study will detect a clinically important treatment difference at two-sided 0.05 significance level on either of the primary outcome measures. The NEADL is based on data from a trial by Logan et al. [45] on a between-group difference in the means of 1.73 and a standard deviation of 5.39 (NEADL score 0–22). Such a change would mean that clinically, an older person who was unable to walk around outside at the beginning of the study, would be able to do so at three months; or a person who may have needed help to do their own shopping at the beginning of the study would no longer require any assistance at three months. Adjustments have been made for drop-out (20%) and non-compliance (10%) based on pilot data [16]. Power analysis was conducted using Power and Precision Ver. 2.1.

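### ANCOVA is named for every secondary outcome, including fall and service-use events and a yes/no-type question; falls could be distorted if observed time differs by arm

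*Protocol article*

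**What the plan says.** The sentence on between-group comparison, in Statistical analysis, reads "Between group differences for primary and secondary outcome measures will be analysed using analysis of covariance (ANCOVA"), and it presents the method as a way to adjust for outside influences. It covers all primary and secondary outcomes. The only other regression in that section looks for predictors of response on the NEADL and LLDI. No count, rate or binary model is named for any secondary outcome.

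Outcome measurement lists the secondary outcomes. Three are scores: FES-I, an SF-36v2 sub-scale and SF-12v2. The others are not:

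- **Falls and service use:** "Falls and community health service use will be recorded using a monthly self report falls calendar and diary". The recording is daily: "Participants will be asked to record daily if they have a fall or not or if they use any community health services for three months".
- **Getting out:** physical activity is measured partly by the question "do you get out of the house as often as you like". The response options are not printed.

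Two further statements bear on time observed. Outcome measurement adds a safeguard: "Participants will be telephoned fortnightly post-discharge to follow up on any falls" and service use. Sample size calculation says: "Adjustments have been made for drop-out (20%) and non-compliance (10%) based on pilot data". The drop-out figure is not split by arm.

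**The concern.** ANCOVA is a linear model for a continuous outcome with roughly constant variance. Fall counts over three months are likely to be skewed, with many zeros and a variance that grows with the mean. Service contacts are also counts. For these outcomes ANCOVA gives an adjusted difference in mean counts, not a rate ratio. For a yes/no item it gives a difference in proportions.

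Time observed matters more. Someone who leaves the study or dies after one month has had a third of the planned time in which to record a fall. Calendars are collected at the final assessment, so a person who drops out may leave only a partial record. If raw counts are compared and one arm is observed for less time, part of the difference in falls is a difference in observation. The arms have different contact with therapists (home visits and support calls against a hospital consultation), so different retention is plausible, although the article does not predict it.

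**Working it through.** **The plan's own figure.** The inputs, from Sample size calculation, are a difference of 1.73, SD 5.39, two-sided 0.05 and 80% power. The number per group is 2 × (1.960 + 0.842)² × (5.39/1.73)² ≈ 152.4, so 153 (154 with the t distribution). Adding 20% + 10% gives 153 × 1.30 = 198.9 and 154 × 1.30 = 200.2, or 398 to 400 in total. The stated 400 reproduces. It rests on the NEADL and is not touched by this point.

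**Exposure arithmetic.** Assume that drop-outs leave evenly over the three months, so each contributes half the time on average. Mean exposure in an arm is then 1 − d/2, where d is the drop-out share. With no true effect, the expected ratio of raw mean counts (intervention to control) equals the ratio of exposures:

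- 20% in both arms: 0.90/0.90 = 1.00
- 25% control, 15% intervention: 0.925/0.875 = 1.057
- 30% control, 10% intervention: 0.95/0.85 = 1.118
- 10% control, 30% intervention: 0.85/0.95 = 0.895

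Each split averages the planned 20%. The splits themselves are assumptions.

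**Simulation, no true effect.** Taken from the document: 200 per arm. Assumed: 0.4 falls per person per three months, overdispersion 1.5, and 1,500 trials per scenario. ANCOVA was run on raw counts, adjusted for baseline falls. The comparator was a log-link count model with log(time observed) as offset and robust standard errors, unadjusted for baseline. It stands in for a negative binomial model.

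| Drop-out, control/intervention | Raw count ratio | ANCOVA type I error | Ratio, offset model | Type I error, offset model |
|---|---|---|---|---|
| 0%/0% | 0.99 | 4.1% | 0.99 | 5.1% |
| 20%/20% | 1.00 | 4.8% | 1.00 | 5.4% |
| 25%/15% | 1.06 | 5.4% | 1.00 | 5.2% |
| 30%/10% | 1.12 | 8.7% | 1.01 | 4.4% |
| 10%/30% | 0.89 | 9.5% | 1.00 | 5.4% |

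The Monte Carlo standard error near 5% is √(0.05 × 0.95/1500) ≈ 0.6 points, so only the last two ANCOVA figures stand clear of nominal.

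**Simulation, true rate ratio 0.70.**

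| Drop-out, control/intervention | Raw count ratio | ANCOVA mean difference | ANCOVA power | Ratio, offset model | Power, offset model |
|---|---|---|---|---|---|
| 0%/0% | 0.71 | −0.116 | 41% | 0.71 | 37% |
| 20%/20% | 0.70 | −0.106 | 38% | 0.70 | 35% |
| 30%/10% | 0.78 | −0.075 | 21% | 0.69 | 36% |

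Balanced loss shrinks the mean difference a little and leaves the ratio alone. Unbalanced loss moves the ratio (0.70 × 0.95/0.85 = 0.78) and halves ANCOVA's power. ANCOVA's small advantage in the first two rows is not like for like, because only ANCOVA was adjusted for baseline falls.

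**Yes/no item.** With 160 per arm (200 less 20%) and 3,000 simulated trials, ANCOVA on a 0/1 outcome rejected a true null in 5.5% of trials at an assumed prevalence of 30%, and in 4.3% at 50%.

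**The case against.** A reader might infer that unequal diary follow-up does bias the falls result. The documents do not support that. They give one overall drop-out figure, say nothing of a difference between arms, and do not say whether falls will be summarised as a count, a rate or faller status. At an assumed 25%/15% split the type I error is essentially nominal.

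Nor is ANCOVA unable to use time observed. It could be run on falls per month, or with days observed as a covariate. The article simply names neither. The direction of any bias is not fixed either: the arm that loses more people appears to have fewer falls only if partial records are counted as complete. If those people are excluded, that does not follow.

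The fortnightly blinded calls, and data linkage for deaths and admissions, should limit partial records and help to date the end of follow-up. Nothing in the article ranks falls as the main safety outcome. An adjusted risk difference for the yes/no item is interpretable and keeps its type I error.

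All of this stands and limits the point. It does not remove it. The article is not silent, leaving the choice to an analysis plan: it names one method for every secondary outcome, and that method fits three of them poorly. An analysis plan with count or logistic models would have to depart from the published sentence.

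**Conclusion.** The point holds as a mismatch between method and outcome type, with a conditional risk of distortion. Bias in falls or service use needs two things together: observed time that differs by arm, and raw counts analysed without a time term. Under an assumed 30%/10% split and no true effect, the raw fall-count ratio is off by 11% to 12% and the type I error is about 9%. With equal drop-out of 20% there is no false effect. These sizes rest on the assumed fall rate, overdispersion, timing of drop-out and split between arms, and on diary loss following the planned drop-out. They were worked for falls only; for service use the exposure arithmetic carries over if contacts accrue evenly over time, but the error rates would depend on its own distribution.

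For the getting-out question the issue is model fit and effect measure only. Severity is moderate, because only secondary outcomes are affected. ANCOVA remains suitable for the NEADL and LLDI.

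**What to change.** Replace the single sentence with a short paragraph by outcome type:

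- **Scores** (NEADL, LLDI, FES-I, SF-12v2 and SF-36v2 scales): keep ANCOVA.
- **Falls and community health service contacts:** negative binomial regression with log(days observed) as offset, adjusted for site and age stratum and, for falls, baseline falls history. Report a rate ratio with its confidence interval. Define days observed as discharge to the last day covered by calendar, diary or telephone call, or to death, up to three months.
- **Getting-out question:** logistic regression, or ordinal if there are more than two response levels, adjusted for the baseline answer. State the response options. The article does not list this question by name in the baseline assessment, so confirm that it is asked then.

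The cost is one paragraph, settled before the data are analysed so that the falls model is not chosen after the results are seen. Daily calendars, fortnightly calls and baseline falls history are already planned, and the sample size does not change.

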### Randomisation

Individual randomisation will occur following baseline assessment, as demonstrated in Figure 1. Participants will be stratified by site and by age (70–84, >84 years). Age stratification has been incorporated as the research group expects that the HOME intervention will have differential effects on these age groups. The randomisation schedule was developed by a researcher not involved in group allocation and using the program STATA ver. 17 and the add-on program Ralloc [24] to generate the random sequence. Once baseline assessments have been completed allocation will be determined by using a password protected website to conceal randomisation. This will be carried out by a researcher not involved in follow up assessment. Occupational therapists administering the experimental and control interventions will not be blind to allocation.

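### The model meant to find predictors of response to HOME is described without any contrast with controls, so as written it finds who recovers, not who benefits

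*Protocol article*

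**What the plan says.** The Statistical analysis section has two parts. The first assigns the between-group comparison of primary and secondary outcomes to ANCOVA. The second states a separate aim: "Multivariate regression modelling will be used to examine predictors of successful response to intervention". For that aim the section fixes two things:

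- Predictors: "Potential predictors measured at baseline are personal characteristics, self efficacy beliefs, sub-domains of perceived health status, functional performance and disability levels".
- Outcome: "clinical improvements in NEADL and LLDI will be inputted as the dependant variable".

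The section does not say whether one arm or both enter the model, and it lists neither group nor a product of group with any predictor. Improvement is not defined there.

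Two other sections bear on the point. On NEADL and LLDI, Outcome measurement says: "These assessments will be completed at baseline and three months post-discharge from hospital". Randomisation explains the age strata by saying that "the research group expects that the HOME intervention will have differential effects on these age groups". No section describes a test of that expectation.

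**The concern.** Response to HOME is the difference that allocation to HOME makes to a participant's outcome. A predictor of response is therefore an effect modifier, and it can be seen only by comparing HOME with control at different levels of the predictor. A regression of improvement on baseline variables answers another question: who improves.

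The two questions can easily diverge here. Baseline is assessed in hospital, and the Background says that function often falls during an admission. Some recovery by three months is plausible in both arms, and its predictors would be reported as predictors of response to HOME. The predictor list also includes "functional performance and disability levels". If these are the baseline NEADL and LLDI scores, the baseline value enters both the predictor and the improvement. The NEADL is bounded at 0 to 22, so high scorers also have little room to improve.

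At stake is the meaning of one subsidiary analysis. Its result could be read as a list of people who benefit from HOME when it is a list of people who recover. It also could not test the differential age effect for which the trial is stratified.

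**Working it through.** **The plan's own figure.** The article states no figure for the predictor model. The only figure that can be reproduced is the sample size, whose inputs are used below: difference 1.73, SD 5.39, two-sided 0.05, power 80%. The normal formula gives n = 2 x (1.96 + 0.84)^2 x 5.39^2 / 1.73^2, which rounds up to 153 per arm. Multiplying by 1.3 for 20% drop-out and 10% non-compliance gives 199 per arm, or 398 in total, close to the stated 400. This does not bear on the point. With 20% drop-out, 200 x 0.8 = 160 per arm are followed up.

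**Step 1: baseline score against change.** Assume that improvement is the three-month score minus baseline, with equal SDs at both times and correlation r. The article gives no r, so a range is used. The slope of change on baseline is then r - 1, and the correlation is -sqrt((1 - r)/2):

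- r = 0.5: slope -0.5, correlation -0.50
- r = 0.7: slope -0.3, correlation -0.39
- r = 0.9: slope -0.1, correlation -0.22

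This arises in both arms, with no effect modification and even with no treatment effect.

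**Step 2: how often a predictor is declared when no one responds differently.** Simulation settings: 1,000 runs each, 320 completers, SD 5.39, and a constant HOME effect of 1.73 for everyone. Change was regressed on the predictor in three ways. The entries are the percentage of runs with p < 0.05.

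| Predictor (assumed correlation) | HOME arm only | Both arms, group main effect | Group-by-predictor test |
|---|---|---|---|
| Baseline score, r = 0.5 | 100 | 100 | 6.0 |
| Baseline score, r = 0.7 | 99.8 | 100 | 4.6 |
| Baseline score, r = 0.8 | 98.4 | 100 | 4.5 |
| Baseline score, r = 0.9 | 81.8 | 98.5 | 4.9 |
| Other prognostic factor, 0.1 with change | 25.5 | 44.3 | 4.2 |
| Other prognostic factor, 0.2 with change | 72.3 | 96.0 | 4.6 |
| Other prognostic factor, 0.3 with change | 97.5 | 100 | 5.9 |

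Only the interaction test keeps to its nominal 5%. The second column already includes a group main effect, so adding group alone does not solve the problem.

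**Step 3: what the choice of outcome changes.** Write the three-month score as Y1 = a + b Y0 + c G + d X + e GX + error, where Y0 is baseline, G is group and X is a predictor. Subtracting Y0 from both sides gives Y1 - Y0 = a + (b - 1) Y0 + c G + d X + e GX + error. Only the coefficient of Y0 moves, by exactly -1. The interaction e is the same for either outcome. The missing group contrast is therefore the core defect, and the change score is secondary.

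**Step 4: precision of the corrected analysis.** For a predictor split 50/50 with 160 per arm:

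- SE of the main effect = 5.39 x sqrt(2/160) = 0.603
- SE of the interaction = 5.39 x sqrt(2/80 + 2/80) = 1.205
- detectable at 80% power, unadjusted = 2.8 x 1.205 = 3.37 points

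Baseline adjustment multiplies the SE by sqrt(1 - r^2):

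- r = 0.5: SE 1.04, detectable 2.9 points
- r = 0.6: SE 0.96, detectable 2.7 points
- r = 0.7: SE 0.86, detectable 2.4 points

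Unadjusted power for an interaction as large as the design effect of 1.73 is about 30% with 320 participants and 36% with 400.

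**The case against.** The strongest reply is that this is a condensed journal article. It names candidate predictors and does not write out a model equation. It cites a methods reference that is not at hand, and its stated aim is compatible with interaction terms that a fuller plan may contain. This stands in part. A reader might infer that the plan rejects an interaction or restricts the model to one arm; the text is silent on both, so neither can be claimed. The simulations show what follows if the description is taken literally, not that the trial team will fit that model. Even so, the article does fix an aim, a predictor set and an outcome, and together these do not identify response to HOME. An analysis that followed the wording would inherit the mismatch.

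Three stronger readings are also tempting:

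- *Coupling with baseline invalidates the whole model.* The documents do not define improvement as three-month minus baseline score. The nearest operational wording, in the cost effectiveness measures, is the proportion with a clinically significant NEADL improvement, which is binary. The correlations in Step 1 would not be the size of the problem for a binary outcome. For a continuous one, Step 3 shows that once the baseline score is a covariate, only its own coefficient is affected. For the other predictors the issue is prognosis.
- *About 3.4 points is the detectable interaction in the corrected model.* That value uses the unadjusted SD, whereas the corrected model adjusts for baseline.
- *The result would decide who is offered home visits.* No section says so. The Discussion ties policy relevance to effectiveness and cost effectiveness, and this analysis lies outside the primary hypotheses and the sample size calculation.

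**Conclusion.** The concern holds as a mismatch between aim and method. As described, the model has no contrast with controls and so cannot show who benefits from HOME, whichever arms are used, nor can it test the expected difference by age. With no true effect modification it would flag the baseline score in about 82% to 100% of analyses. A purely prognostic factor would be flagged in about 26% to 100%, depending on its strength and the arms used. The interaction test gives 4% to 6%.

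These rates assume a continuous change score, equal SDs, 320 completers, baseline/follow-up correlations of 0.5 to 0.9 and prognostic correlations of 0.1 to 0.3. The article gives none of these correlations. The logical point depends on none of these values. The analysis is subsidiary, and the primary between-group ANCOVA is unaffected.

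**What to change.** Reword the predictor analysis as follows:

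- Fit it in both arms, with baseline score, group, each candidate predictor and group-by-predictor terms, taking the age stratum first because the protocol already expects an effect there.
- Preferably use the three-month score as the outcome, and avoid a dichotomised improvement.
- Interpret only the interaction terms as predictors of response, report them with confidence intervals and label the analysis exploratory.

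If the team does not want interaction terms, it should rename the analysis as one of prognostic factors and drop the reference to response to the intervention.

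The change is to wording and needs no new data. The cost is precision. Even after baseline adjustment, an evenly split predictor would need an interaction of about 2.4 to 2.9 NEADL points, well above the 1.73 on which the trial is sized. An uneven split, as the age strata may be, would need more. Fewer predictors will be declared, and a null interaction should not be read as evidence of a uniform effect.

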### Economic analysis

Incremental cost effectiveness analysis, that is the difference in mean cost to mean difference in effectiveness, will be the primary economic outcome [44]. Incremental cost per clinically significant improvement in the NEADL score will be determined, then incremental cost per QALY. Incremental QALY will be the sum of difference in duration of survival as weighted by quality of life between the two trial groups at three months. Confidence intervals will be calculated using Fieller’s method, and results will be presented in the form of a cost effectiveness acceptability curve [41]. A sensitivity analysis will be conducted to determine the ability to generalise results. The net costs and net effectiveness QALYS of HOME will be compared to hospital control group as expressed as incremental cost per QALY gained.

### Sample size calculation

A total of 400 participants will enter this two-armed, parallel-design study (200 per group). The probability is 80% that the study will detect a clinically important treatment difference at two-sided 0.05 significance level on either of the primary outcome measures. The NEADL is based on data from a trial by Logan et al. [45] on a between-group difference in the means of 1.73 and a standard deviation of 5.39 (NEADL score 0–22). Such a change would mean that clinically, an older person who was unable to walk around outside at the beginning of the study, would be able to do so at three months; or a person who may have needed help to do their own shopping at the beginning of the study would no longer require any assistance at three months. Adjustments have been made for drop-out (20%) and non-compliance (10%) based on pilot data [16]. Power analysis was conducted using Power and Precision Ver. 2.1.

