**Methods/design:**

400 participants admitted to participating hospitals will be recruited. Participants will be 70 years of age and over, have no significant cognitive impairment and be independently mobile at discharge. This study protocol was approved by the ethics committee of Ryde Rehabilitation Human Research Ethics Committee, Western Sydney Local Health District (Westmead Campus) Human Research Ethics Committee, Alfred Health Human Research ethics committee for the randomised trial and NSW Population and Health Service Human Research Ethics Committee for data linkage. Participants will provide informed written consent.

Participants will be randomly allocated to the intervention or control group. The intervention group will receive discharge planning therapies primarily within their home environment while the control group will receive an in-hospital consultation, both provided by trained occupational therapists. Primary outcome measures will be the Nottingham Extended Activities of Daily Living Scale (NEADL) and the Late Life Disability Index (LLDI) which will measure functional independence, and participation and limitation in daily life activities.

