Results of two feasibility trials [16,18] indicate that a large randomised trial to determine the effectiveness of occupational therapy discharge planning is achievable. These and other studies [15,19] support the necessity of evaluating cost effectiveness of occupational therapy discharge planning in addition to clinical effectiveness of home assessments in reducing functional difficulties. Through cost effectiveness analysis, decisions can be made as to whether a new intervention is effective and whether or not benefits are cost efficient compared to current practice [20]. Since occupational therapy treatment focuses on increasing or maintaining independence, there is a potential for discharge planning to reduce healthcare costs, including readmission to hospital, decreased community health service use and delay nursing care facility admission.

Research must be conducted to identify the best practice for occupational therapy discharge planning and this should be evaluated for its effectiveness and cost effectiveness. The HOME intervention has been developed from recommendations in occupational therapy literature as a method of comprehensive discharge planning and now requires evaluation. The primary aim of this study is to determine the effectiveness of occupational therapy discharge planning in reducing functional difficulties. The primary hypotheses is that people who receive the HOME intervention will have (i) higher levels of functional independence three months after discharge then the control group and (ii) higher levels of participation and resumption of usual life activities compared to the control group.

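### The 80% power claim covers both primary outcomes but was calculated for the NEADL only, and no rule says whether one or both must succeed

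*Protocol article*

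**What the plan says.** The abstract (Methods/design) sets two primary outcomes: "Primary outcome measures will be the Nottingham Extended Activities of Daily Living Scale (NEADL) and the Late Life Disability Index (LLDI"). The Outcome measurement section repeats this and adds that "participation and limitation in activities of daily living will be assessed using the Late Life Disability Index (LLDI"). It does not say how many LLDI scores are primary.

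The end of the Background section gives two primary hypotheses joined by a conjunction. The first is better functional independence at three months than "the control group and (ii) higher levels of participation and resumption of usual life activities".

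The Sample size calculation section makes the power claim: "The probability is 80% that the study will detect a clinically important treatment difference". The same sentence then fixes the test level and the outcomes that the claim covers: "at two-sided 0.05 significance level on either of the primary outcome measures". It then gives one set of inputs, for the NEADL: a "between-group difference in the means of 1.73 and a standard deviation of 5.39". The size is stated as "A total of 400 participants will enter this two-armed, parallel-design study (200 per group"), and "Adjustments have been made for drop-out (20%) and non-compliance (10"%).

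The Statistical analysis section applies ANCOVA to all primary and secondary outcomes. It gives no significance level, no division of alpha and no order of testing.

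**The concern.** There are two separate problems.

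- **Unsupported power claim.** The 80% figure is asserted for both primary outcomes, but a difference and SD are given for only one. A reader cannot tell what LLDI effect the trial is able to detect.
- **Open success rule.** With two primary outcomes, 0.05 attached to each, and no statement of what counts as success, the design's error rate and power are not fixed. If one significant result is enough, the overall type I error exceeds 5%. If both are needed, the power to succeed is below 80%.

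The practical risk is a split result. If one primary outcome is significant and the other is not, nothing in the protocol says whether the trial succeeded, so the question could be settled after the data are seen. The abstract expects the results to bear directly on practice and policy, so this should be settled in advance.

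**Working it through.** **Inputs from the protocol (Sample size calculation).** NEADL difference 1.73, SD 5.39, two-sided alpha 0.05, power 80%, 200 per group, drop-out 20%, non-compliance 10%. LLDI difference and SD: none given. Correlation between the two outcomes: none given, so 0 to 0.8 is assumed below.

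**Step 1. Reproduce the 200 per group.**

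- Standardised difference: 1.73 / 5.39 = 0.321.
- n per arm = 2 × (1.960 + 0.842)² / 0.321² = 152.4, so 153 (154 with the t distribution).
- Inflation by 20% + 10%: 153 × 1.30 = 199 and 154 × 1.30 = 200.

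This matches the stated 200. Inflating by 1.2 × 1.1 gives 202, which is also close. The stated size is thus the NEADL calculation at the whole of 0.05, with nothing set aside for a second primary test.

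**Step 2. What the LLDI claim would need.** With 20% drop-out, 200 × 0.8 = 160 per arm are evaluable. The standardised effect detectable with 80% power at 0.05 is (1.960 + 0.842) × √(2/160) = 0.313. The protocol gives nothing from which to judge whether an LLDI effect of about 0.31 SD is plausible or clinically important.

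**Step 3. If a win on either outcome counts, each tested at 0.05.** For independent tests the familywise error is 1 − 0.95² = 0.0975. For correlated tests it is 1 − P(|Z₁| < 1.96 and |Z₂| < 1.96), with Z₁ and Z₂ bivariate normal.

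**Step 4. If both must be significant.** Assume the LLDI also has 80% power. Joint power is 0.8 × 0.8 = 0.64 if independent. Otherwise it is P(Z₁ < 0.842 and Z₂ < 0.842), bivariate normal.

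| Assumed correlation | Familywise error, either counts | Joint power, both required |
|---|---|---|
| 0 | 9.8% | 64% |
| 0.5 | 9.1% | 69% |
| 0.8 | 7.8% | 73% |

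**Step 5. What an alpha split would cost.** At 0.025, the NEADL needs 2 × (2.241 + 0.842)² / 0.321² = 184.5, so 185 evaluable per arm against 153. With the 1.30 inflation, 185 × 1.30 = 240.5, so 241 per arm or 482 in total. Keeping 160 evaluable per arm, the non-centrality is 0.321 × √(160/2) = 2.871. NEADL power is then:

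- at 0.05: Φ(2.871 − 1.960) = 82%;
- at 0.025: Φ(2.871 − 2.241) = 74% (73% with the t distribution).

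These power figures allow for drop-out but not for dilution of the effect by non-compliance.

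**The case against.** The best defence is that this is a condensed article. Success rules and multiplicity procedures are often left to an analysis plan, and the Statistical analysis section sets no significance level. The 0.05 per outcome comes from the power statement, not from a stated testing rule. This has force: the absence of a multiplicity procedure would not be a finding by itself. But the article goes further. It asserts 0.05 and 80% for both measures, and it commits a sample size that uses the full 0.05 on the NEADL. A later plan that split alpha would bring NEADL power below the stated 80% at 160 evaluable per arm (Step 5). The LLDI power claim lacks a basis whatever a later plan says.

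A reader might infer three stronger things that the document does not support.

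- **That the power statement contradicts the hypotheses.** The power statement can mean each measure taken separately, and the conjunction in the Background may only list two hypotheses without requiring both. The passages are compatible on that reading. This is an unresolved ambiguity, not a proven contradiction.
- **That there are three or more primary tests.** The LLDI is said to cover participation and limitation, which suggests two scores, but the protocol names two measures and does not say how many LLDI scores are primary. The independent-test figure for three tests, 1 − 0.95³ = 14.3%, applies only if the LLDI yields two primary scores.
- **That the stated size of 400 is wrong.** It reproduces from the NEADL inputs, and this point gives no reason to correct it.

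The joint-power figures also depend on an LLDI power that the protocol does not support, so they are illustrations.

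**Conclusion.** The concern holds in a limited form. The 80% power claim is supported for the NEADL only, and the protocol leaves open what counts as success on two primary outcomes.

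The consequence depends on the rule eventually adopted. An either-counts rule with 0.05 per test carries a familywise error of about 8% to 10%. A both-required rule keeps the error controlled but gives joint power of about 64% to 73%. The first range rests on an assumed correlation of 0.8 to 0; the second rests on a correlation of 0 to 0.8 and on an LLDI power of 80%. Under each rule one of the two advertised properties, 5% error or 80% power, is lost.

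The protocol does not state either rule, so it cannot be said that the trial will declare success on whichever outcome crosses 0.05. The point should be fixed, but it does not invalidate the design.

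**What to change.** Three changes of wording, before any outcome data are examined:

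1. In the Sample size calculation section, limit the 80% power statement to the NEADL, or add the LLDI difference and SD that support it.
2. In the Outcome measurement section, name the LLDI score or scores that are primary.
3. State the success rule, with familywise error held at two-sided 0.05.

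Several rules would do, and the choice is the sponsor's:

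- **Fixed sequence.** Test the NEADL at 0.05, then the LLDI at 0.05 only if the NEADL is significant. This needs no more participants and loses no NEADL power. Its cost is that a benefit on the LLDI alone could not be claimed as confirmatory, although the protocol now gives the two outcomes equal standing.
- **Holm.** This suits an intention that either outcome should count. It costs some power: with 160 evaluable per arm, NEADL power is about 73% to 74% when tested at 0.025. That is the worst case, since Holm allows 0.05 once the LLDI has been rejected.
- **Both required, each at 0.05.** No alpha adjustment is needed, but the joint power should be stated, which again requires LLDI inputs.

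If more than one LLDI score is primary, the rule must cover those scores too, in a stated order or by Holm.
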